| Feasibility counts Feasibility counts presented below are based on the January 2018 version of the CPRD GOLD primary care database.  We identified 65,136 women who had a diagnosis of breast cancer (Read codes provided in appendix 2) while aged between 18 and 80 years, registered with a primary care practice contributing with data to CPRD, and whose individual records were acceptable for research. Non-interrupted one year of follow up before the cancer diagnosis (index date) was not available for 6,757 women, and 6,044 women were further excluded because they had a lifetime diagnosis of severe mental illness or another cancer before their breast cancer diagnosis (see section J for the inclusion and exclusion criteria).  Hence, 52,335 women with a history of breast cancer were identified as eligible for this study; the table below provides details of the distribution by age and calendar period of diagnosis.  Table 1 Distribution of women with breast cancer history who are eligible for this study, by age and calendar period of diagnosis.   \|  \| **N** \| **%** \| \| --- \| --- \| --- \| \|  \|  \|  \| \| **All study participants** \| **52,335** \| **(100.0)** \| \|  \|  \|  \| \| **Calendar period of diagnosis** \|  \|  \| \| 1989-1994 \| 3,184 \| (6.1) \| \| 1995-1999 \| 4,768 \| (9.1) \| \| 2000-2004 \| 10,934 \| (20.9) \| \| 2005-2009 \| 14,705 \| (28.1) \| \| 2010-2014 \| 13,805 \| (26.4) \| \| ≥2015 \| 4,939 \| (9.4) \| \|  \|  \|  \| \| **Age at diagnosis (years)** \|  \|  \| \| 18-24 \| 24 \| (0.1) \| \| 25-34 \| 771 \| (1.5) \| \| 35-44 \| 4,916 \| (9.4) \| \| 45-54 \| 12,235 \| (25.3) \| \| 55-64 \| 14,910 \| (28.5) \| \| 65-74 \| 12,811 \| (24.5) \| \| 75-80 \| 5,668 \| (10.8) \| \|  \|  \|  \|   A comparison group of women without cancer (4 controls per breast cancer case) will be randomly selected from the same data source, same primary care practice and within a 3-year age range.  Appendix 2 provides the list of Read codes used to identify women with a history of breast cancer in the CPRD GOLD primary care database. The list of Read codes used to identify cancer diagnoses other than the breast one (exclusion criterion) has been published elsewhere [14]. A provisional list of Read codes to identify women with several mental illnesses (exclusion criterion) was defined for the purpose of this calculation; the final list will be refined in due course. |

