| Sample size considerations Table 2 shows the minimum relative risk that could be detected with the 52,335 women identified in the CPRD GOLD primary care database, for different probabilities of type I (α) and type II error (β). These estimates were obtained with the command ‘power’ in Stata v15 [15].  Table 2 Minimum RR that can be detected with the 52,355 women with a history of breast cancer and 209,420 women who did not have cancer, for different probabilities of type I and type II errors, and baseline risk of the outcomes.   \| **Outcome** \| **α** \| **β** \| **% of outcome in unexposed group [ref]** \| **Min. HR possible to be estimated** \| \| **RR/HR estimated in other studies [ref]** \| \| \| --- \| --- \| --- \| --- \| --- \| --- \| --- \| --- \| \|  \|  \|  \|  \|  \| \|  \| \| \| **Primary outcomes** \|  \|  \|  \|  \| \|  \| \| \|  \|  \|  \|  \|  \| \|  \| \| \| **Anxiety, diagnoses** \| **0.05** \| **0.20** \| **5 [7]** \| **1.05** \| \| 1.06 [7]  1.08 [7]  1.22 [11]  1.25 [8] \| \| \| **0.01** \| **0.20** \| **5 [7]** \| **1.06** \| \| \| **0.05** \| **0.10** \| **5 [7]** \| **1.06** \| \| \| 0.01 \| 0.10 \| 5 [7] \| 1.07 \| \| \|  \|  \|  \|  \| \| \| **0.05** \| **0.20** \| **20 [11]** \| **1.02** \| \| \| **0.01** \| **0.20** \| **20 [11]** \| **1.03** \| \| \| **0.05** \| **0.10** \| **20 [11]** \| **1.03** \| \| \| **0.01** \| **0.10** \| **20 [11]** \| **1.03** \| \| \|  \|  \|  \|  \|  \| \|  \| \| \| **Anxiety, prescription of**  **anxiolytics** \| **0.05** \| **0.20** \| **3 [10]** \| **1.07** \| \| 1.08 [7]  2.52 [10] \| \| \| **0.01** \| **0.20** \| **3 [10]** \| **1.08** \| \| \| **0.05** \| **0.10** \| **3 [10]** \| **1.08** \| \| \| 0.01 \| 0.10 \| 3 [10] \| 1.09 \| \| \|  \|  \|  \|  \| \| \| **0.05** \| **0.20** \| **8 [7]** \| **1.04** \| \| \| **0.01** \| **0.20** \| **8 [7]** \| **1.05** \| \| \| **0.05** \| **0.10** \| **8 [7]** \| **1.05** \| \| \| **0.01** \| **0.10** \| **8 [7]** \| **1.06** \| \| \|  \|  \|  \|  \|  \| \|  \| \| \| **Depression, diagnoses** \| 0.05 \| 0.20 \| 3 [11] \| 1.07 \| \| 1.06 [7]  1.39 [9]  1.49 [8]  1.94 [11] \| \| \| 0.01 \| 0.20 \| 3 [11] \| 1.08 \| \| \| 0.05 \| 0.10 \| 3 [11] \| 1.08 \| \| \| 0.01 \| 0.10 \| 3 [11] \| 1.09 \| \| \|  \|  \|  \|  \| \| \| **0.05** \| **0.20** \| **9 [7]** \| **1.04** \| \| \| **0.01** \| **0.20** \| **9 [7]** \| **1.05** \| \| \| **0.05** \| **0.10** \| **9 [7]** \| **1.04** \| \| \| **0.01** \| **0.10** \| **9 [7]** \| **1.05** \| \| \|  \|  \|  \|  \|  \| \|  \| \| \| **Depression, prescription of**  **antidepressants** \| **0.05** \| **0.20** \| **2 [10]** \| **1.08** \| \| 1.16 [7]  1.95 [10] \| \| \| **0.01** \| **0.20** \| **2 [10]** \| **1.10** \| \| \| **0.05** \| **0.10** \| **2 [10]** \| **1.09** \| \| \| **0.01** \| **0.10** \| **2 [10]** \| **1.11** \| \| \|  \|  \|  \|  \| \| \| **0.05** \| **0.20** \| **20 [7]** \| **1.02** \| \| \| **0.01** \| **0.20** \| **20 [7]** \| **1.03** \| \| \| **0.05** \| **0.10** \| **20 [7]** \| **1.03** \| \| \| **0.01** \| **0.10** \| **20 [7]** \| **1.03** \| \| \|  \|  \|  \|  \|  \| \|  \| \| \| **Secondary outcomes *** \|  \|  \|  \|  \| \|  \| \| \|  \|  \|  \|  \|  \| \|  \| \| \| **Sexual dysfunction** \| 0.05 \| 0.20 \| 4.1 [16] \| 1.06 \| \| 1.03 [16]  2.27 [17] \| \| \| 0.01 \| 0.20 \| 4.1 [16] \| 1.07 \| \| \| 0.05 \| 0.10 \| 4.1 [16] \| 1.07 \| \| \| 0.01 \| 0.10 \| 4.1 [16] \| 1.08 \| \| \|  \|  \|  \|  \| \| \| 0.05 \| 0.20 \| 9.1 [17] \| 1.04 \| \| \| 0.01 \| 0.20 \| 9.1 [17] \| 1.05 \| \| \| 0.05 \| 0.10 \| 9.1 [17] \| 1.04 \| \| \| 0.01 \| 0.10 \| 9.1 [17] \| 1.05 \| \| \|  \|  \|  \|  \|  \| \|  \| \| \| **Suicide** \| 0.05 \| 0.20 \| 0.0008** [18] \| 1.47 \| \| 1.37 [18]  1.6 [19] \| \| \| 0.01 \| 0.20 \| 0.0008** [18] \| 1.60 \| \| \| 0.05 \| 0.10 \| 0.0008** [18] \| 1.57 \| \| \| 0.01 \| 0.10 \| 0.0008** [18] \| 1.70 \| \| \|  \|  \|  \|  \|  \| \|  \| \| \| **Fatal and**  **non-fatal self-harm** \| 0.05 \| 0.20 \| 0.005 [18, 20] \| 1.17 \| \| 1.03 [21]  1.37 [18] \| \| \| 0.01 \| 0.20 \| 0.005 [18, 20] \| 1.21 \| \| \| 0.05 \| 0.10 \| 0.005 [18, 20] \| 1.20 \| \| \| 0.01 \| 0.10 \| 0.005 [18, 20] \| 1.24 \| \| \|  \|  \|  \|  \|  \| \|  \| \| \| **Sleep disturbances** \| 0.05 \| 0.20 \| 50 [22] \| 1.01 \| \| 0.8 [22] \| \| \| 0.01 \| 0.20 \| 50 [22] \| 1.02 \| \| \| 0.05 \| 0.10 \| 50 [22] \| 1.02 \| \| \| 0.01 \| 0.10 \| 50 [22] \| 1.02 \| \| \|  \|  \|  \|  \|  \| \|  \| \| \| **Prescription of hypnotics** \| **0.05** \| **0.20** \| **4 [23]** \| **1.06** \| \| 3.75 [23] \| \| \| **0.01** \| **0.20** \| **4 [23]** \| **1.07** \| \| \| **0.05** \| **0.10** \| **4 [23]** \| **1.07** \| \| \| **0.01** \| **0.10** \| **4 [23]** \| **1.08** \| \| \|  \|  \|  \|  \|  \| \|  \| \| \| **Mild cognitive impairment** \| **0.05** \| **0.20** \| **5 [24]** \| **1.05** \| \| 1.58 [25]  1.60 [26]  2.43 [24]  3.67 [27] \| \| \| **0.01** \| **0.20** \| **5 [24]** \| **1.06** \| \| \| **0.05** \| **0.10** \| **5 [24]** \| **1.06** \| \| \| **0.01** \| **0.10** \| **5 [24]** \| **1.07** \| \| \|  \|  \|  \|  \| \| \| **0.05** \| **0.20** \| **19 [26]** \| **1.02** \| \| \| **0.01** \| **0.20** \| **19 [26]** \| **1.03** \| \| \| **0.05** \| **0.10** \| **19 [26]** \| **1.03** \| \| \| **0.01** \| **0.10** \| **19 [26]** \| **1.04** \| \| \|  \|  \|  \|  \| \|  \| \|  \| \|   HR – hazard ratio. RR – risk ratio. Bold is used to denote where the minimum risk ratio that could be detected with the available sample size is lower than the lowest estimate reported in the literature.  * No population-based studies have been identified reporting the relative risk of sexual dysfunctions, pain, fatigue, sleep disorders or cognitive dysfunction in breast cancer survivors compared to the non-cancer female population. Thus, the relative risk reported in the column for the other studies comes from studies involving convenience samples of cancer survivors. Pain and fatigue are often evaluated using psychometric instruments whose mean scores are summarised as means for between-group comparisons; no studies were identified providing data for the prevalence of pain and fatigue in breast cancer survivors and in women who did not have cancer, and thus these two outcomes were not included in the table.  ** Calculated as the proportion of suicides in the exposed group divided by the inverse of the standardised mortality ratio reported in the original study.  The available sample size is expected to be sufficient for detecting clinically significant increases of anxiety and depression (primary outcomes) in breast cancer survivors compared to the women who did not have cancer.  For the secondary outcomes, sample size is likely to be enough to assess differences in sleep disturbance measured by hypnotics’ prescription, and mild cognitive impairment. However, the available sample size will have relatively small power to detect small differences in suicide between women with history of breast cancer and those who did not have cancer, because this is a rare outcome, but we will still have enough power to detect associations of a magnitude seen in some previous studies; data from our analysis can also contribute to future meta-analyses. |

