| Definition of the Study population Breast cancer cohort  The study population will consist of all adult women recorded in the CPRD GOLD primary care database as having had an incident breast cancer (Read codes provided in appendix 2) diagnosed during up-to-standard follow-up and prior to the most recent version of the CPRD GOLD primary care database available after all approvals have been obtained.  Inclusion criteria:   1. Female sex, aged ≥18 years; 2. Recorded with a breast cancer diagnosis during CPRD follow-up; 3. Clinical record with at least 12 months of uninterrupted up-to-standard data quality for research (as measured by CPRD) before the breast cancer diagnosis date (to ensure the cancer record represents incident disease).   Exclusion criteria:   1. Diagnosis of severe mental illness before the breast cancer diagnosis (i.e. organic mental disorder, mental disorders due to substances, schizophrenia, delusional disorders, or manic or bipolar episodes) (a provisional list of Read codes was defined for feasibility counts); 2. History of the specified mental health outcome in analysis in the year before the breast cancer diagnosis (list of Read codes to be defined in objective 1 of this study); 3. Diagnosis of any other cancer prior to breast cancer (Read codes available from Ranopa et al. [14]). |
| Selection of comparison group(s) or controls Non-cancer comparison cohort  A comparison cohort will be assembled by randomly selecting, for each index case, up to 4 women of similar age (3-year range), attending the same GP practice, but with no history of cancer at the index date. Matching will also consider the eligibility of the patients’ data for linkage, to ensure that matched-sets have the same probability of having had the information recorded when conducting sub-set analysis using linked data. Controls will be selected using nearest neighbour matching methods without replacement [29]. Women in the non-cancer comparison cohort who meet one or more exclusion criteria will be excluded, as well as their index case.  Women diagnosed with breast cancer during the follow up period will be censored from the unexposed group at the date of the cancer diagnosis, but will be eligible to separately contribute in the exposed group from this date (with corresponding unexposed matches). |

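### One ineligible comparison woman removes an eligible breast cancer case and so her whole matched set; the resulting loss is not allowed for in the feasibility count or the sample size

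*Protocol*

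**What the plan says.** Under selection of comparison group(s) or controls, the Protocol draws, "for each index case, up to 4 women of similar age (3-year range), attending the same GP practice", women with no cancer history at the index date. Linkage eligibility is also considered, and matching is nearest-neighbour without replacement. The Study Design section adds 12 months of up-to-standard data. The selection step mentions neither severe mental illness nor a prior-year outcome. The same paragraph then says: "Women in the non-cancer comparison cohort who meet one or more exclusion criteria will be excluded, as well as their index case". No re-draw is described, and nothing keeps the case in when other eligible matches remain.

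The second exclusion criterion, under definition of the study population, is "History of the specified mental health outcome in analysis in the year before the breast cancer diagnosis". The rule therefore operates separately for each outcome.

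The feasibility section concludes: "Hence, 52,335 women with a history of breast cancer were identified as eligible for this study". That count comes before any outcome-specific exclusion and before matching. The Table 2 caption uses "52,355 women with a history of breast cancer and 209,420 women who did not have cancer", which is four comparison women for every case (and prints a case count that differs from the feasibility count by 20). Under specific aim 2, the main model is a Cox regression stratified on matched set.

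**The concern.** A matched cohort needs only the ineligible comparison woman removed or replaced. Removing her index case as well discards an exposed woman who meets every criterion herself. In a set-stratified Cox model, a set without its exposed member carries no information on exposure, so her remaining eligible matches are lost too. The Protocol gives no reason for this.

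Three things are at stake.
- **Precision.** The number of cases analysed falls short of the number behind the feasibility and sample size statements.
- **Representativeness.** Sets survive preferentially in practices, age groups and periods where the outcome is seldom recorded. Descriptive rates, and the incidence of complications in survivors under specific aim 3, would be affected if computed in the retained cohort.
- **Visibility.** Specific aim 2 plans to count women excluded for their own prior-year outcome. A case removed because of a comparison woman's history does not clearly fall in that count.

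**Working it through.** **Inputs.** Cases: 52,335 (feasibility counts). Comparison women per case: up to 4. Table 2 total: 52,355 + 209,420 = 261,775. Table 2 percentages for the primary outcomes, in unexposed women in other studies: anxiety diagnoses 5% and 20%, anxiolytics 3% and 8%, depression diagnoses 3% and 9%, antidepressants 2% and 20%. The Protocol gives no prior-year prevalence in comparison women, so these percentages stand in for p as an assumption.

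**Table 2 reproduced.** The Cox formula is HR = exp[(z_α/2 + z_power)/√(N·p·a(1−a))], where a is the exposed fraction. With N = 261,775, p = 5%, α = 0.05 two-sided, β = 0.20 and a = 0.5, it gives exp(2.80/√3,272) = 1.050, against 1.05 printed. Of 52 cells tested this way, 48 match to rounding and the other 4 are within 0.01. The planned 1:4 split (a = 0.2) gives 1.063 for the same cell. Under either split, N is the full set of cases with four comparison women each, so no loss is built in.

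**Share of cases lost.** A case survives only if all m of her comparison women are eligible. With independent comparison women, loss = 1−(1−p)^m. At m = 4, for example, 1−0.95⁴ = 1−0.8145 = 18.5%.

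**Interval width.** Information is proportional to the number of complete sets, so relative to full replacement the interval on the log hazard ratio widens by 1/√[(1−p)⁴] = (1−p)⁻².

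| p | Cases lost | Kept of 52,335 | Interval widening | Min. HR, 1:4 split, no loss | Min. HR, rule as written |
|---|---|---|---|---|---|
| 2% | 7.8% | 48,272 | 1.04 | 1.102 | 1.106 |
| 5% | 18.5% | 42,627 | 1.11 | 1.063 | 1.070 |
| 9% | 31.4% | 35,889 | 1.21 | 1.047 | 1.057 |
| 20% | 59.0% | 21,436 | 1.56 | 1.031 | 1.049 |

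Minimum HRs use α = 0.05 and β = 0.20, and let p serve both as prior-year prevalence and as outcome risk. The kept counts are taken before a case's own prior-year exclusion, for which the Protocol gives no figure.

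**Sensitivity.**
- Correlation within sets (beta-binomial, intraclass correlation 0.01 to 0.10): the loss is 16–18% at p = 5% and 53–58% at p = 20%.
- Two matches instead of four: 9.8% and 36%.
- Severe mental illness, if also applied after matching, adds to p and is not in the table.
- The sensitivity analysis requiring five outcome-free years can only raise p.

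**Dropping only the ineligible comparison woman.** A case is then lost only if all four matches are ineligible, which has probability p⁴: 0.0006% at 5% and 0.16% at 20%. Minimum HRs (1:4 before drops) are 1.064 at 5% and 1.032 at 20%, almost the no-loss values.

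**The case against.** The strongest objection concerns size. Table 2's percentages are outcome frequencies from other studies with no stated time window, not one-year histories in CPRD. The 20% figures come from a nationwide study in Taiwan (anxiety diagnoses) and from antidepressant prescribing. The simpler algorithm accepts prescriptions only alongside a recent symptom code, so prescribing is a poor stand-in. This stands: every percentage above is conditional. A reader might infer that at least a fifth of cases go. Table 2's own 2% and 3% rows give 7.8% and 11.5%, so that is not a floor. A reader might also infer that almost all cases go for very common outcomes. That rests on one row, sleep disturbance at 50% (93.75% lost); hypnotic prescription, at 4%, gives 15.1%.

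Second, a reader might infer a biased hazard ratio. Whole sets are removed and the model compares women within sets, so surviving comparisons remain within practice and age. No bias is demonstrated. Outcome-specific cohorts would arise from the second exclusion criterion in any case.

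Third, the sample size conclusion for anxiety and depression is not overturned by this rule. With the 1:4 split, the minimum HR at 20% stays below 1.06, the lowest anxiety estimate in Table 2. At 5% it already exceeds 1.06 before the rule acts.

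Fourth, the order of steps is inferred, since the Protocol does not date each exclusion. But if all screening preceded matching, the sentence would have nothing to act on. If the intention was to drop the comparison women of an excluded case, the sentence says the reverse. It needs changing on either reading.

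**Conclusion.** The point holds. As written, the rule discards eligible cases, and with them their matched sets, for no stated benefit. For the primary outcomes the loss would be about 8% to 59%, and intervals 1.04 to 1.56 times wider than with full replacement. These sizes assume that prior-year prevalence lies in Table 2's 2% to 20% range, that each case has four independent comparison women, and that ineligible women are neither screened out before matching nor replaced. Fewer matches or correlated sets reduce the loss; applying severe mental illness after matching increases it. Even at 2%, 52,335 − 48,272 = 4,063 cases would go. The harm shown is to precision and representativeness. The documents support neither a fixed loss figure nor a claim of bias in the set-stratified hazard ratio.

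**What to change.** Apply all exclusion criteria, including the outcome-specific prior-year one, to potential comparison women before matching. If exclusion has to follow matching, drop only the ineligible comparison woman and keep the case with her remaining or replacement matches. Delete the clause that removes the index case, and state that a set is dropped only when the index case herself is ineligible or no eligible match remains. Report, for each outcome, the number of sets lost and the distribution of matches per case.

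The cost is one sentence in the Protocol and the order of two programming steps, before extraction. Some sets will have fewer than four comparison women, which the existing upper limit of four already permits and the stratified model can handle.
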